**Table 3 Tab3:**
[figure not shown]
Key factors associated with CRC screening completion

Other participant-level factors that will be measured via targeted questions in the baseline and 12-month questionnaires include current health, environmental resources, sociodemographics, and personal health. Current psychological health will be measured through the Brief Symptom Inventory (BSI-18) [38]. Other PCP-level factors that will be evaluated include demographics, experience and comfort level providing care to cancer survivors, and knowledge about the healthcare needs of childhood cancer survivors.

##### Moderators and mediators

Another secondary effectiveness outcome is the assessment of potential moderators and mediators [39]. In this study, the potential moderators include patient characteristics, such as age, gender, educational attainment, health insurance coverage, types of insurance, chronic health conditions, and race/ethnicity as well as PCP factors such as knowledge, years in practice, and practice setting. The potential mediators may include the patient’s perception of involvement in decision-making, health insurance coverage, and whether the patient reviewed the study resources and videos. We will measure these moderators and mediators via the patient questionnaires, PCP questionnaires, and previously collected data from the CCSS.

##### Cost and cost effectiveness

The final secondary effectiveness outcomes are the cost and cost-effectiveness of the intervention; these will be measured by estimating intervention costs and the costs of subseuqnt health services attributable to the intervention. Costs for each component of the intervention (e.g. materials, text messaging design, etc.) will be collected to estimate the cost per person. These costs will be tracked by the study team via study logs and expense reports. In the 12-month survey, we will ask participants about routine or acute medical visits, whether any visit was for gastrointestinal symptoms or conditions or concern about CRC risk, and whether such visits occurred before or after screening, among those who report colonoscopy or multitarget stool DNA test. This data will allow us to quantify the costs of health care services whose use may be attributable to the intervention. Incremental cost-effectiveness ratios will be estimated as the incremental cost per additional participant screened by 12 months, comparing the three study arms.

#### Implementation outcome

We will employ a mixed methods approach to assessing the implementation process from both the participant and the provider perspective.

##### Barriers and facilitators

The secondary implementation outcome is the assessment of barriers and facilitators to the uptake of the intervention. The CFIR provides a structure for evaluating an implementation process [16]. We selected constructs from each of the 5 major CFIR domains (intervention characteristics, outer setting, inner setting, characteristics of individuals and process) as they relate to our intervention (Table 4). PCPs will be asked CFIR questions as part of the 12-month questionnaire and as a component of the end of study interview. In order to develop a more comprehensive understanding of the barriers and facilitators to the implementation of the intervention, we have also included CFIR questions in the 12-month questionnaires and interviews for the participants.

**Table 4 Tab4:**
[figure not shown]
CFIR items for participants and primary care providers

A sample of 20 participants in each intervention arm will be selected for the CFIR interviews. Interviewees will be selected based on their CRC screening behavior since enrolling on the study. In each intervention arm,10 participants who completed CRC screening and 10 participants who did not complete CRC screening will be interviewed. Similarly, a sample of 20 PCPs from each intervention arm will be selected for a CFIR interview. In each intervention arm, 10 PCPs of participants who completed CRC screening since joining the study, and 10 PCPs of participants who did not complete CRC screening since joining the study will be interviewed. Interviews will be conducted and recorded via Zoom, and the study team will transcribe all interviews using Temi, a speech transcription service available online.

### Data sources

We will use a REDCap database, DatStat database, questionnaires, interviews, medical records, previously collected CCSS data, and study logs to collect data for the ASPIRES study. At the conclusion of the study, the statistics team at Memorial Sloan Kettering will have access to the final trial dataset.

#### REDCap database

Personnel at the University of Chicago will manage a secure REDCap database which will contain PCP and medical office staff questionnaire data, medical record confirmation results, all interview transcripts, and select participant questionnaire data. The PROMIS [36, 37], PAM [33], and BSI-18 [38] surveys are components of the participant baseline and 12-month questionnaires; these surveys will be scored, and the scores will be stored in the REDCap database.

#### DatStat database

St. Jude personnel will maintain the DatStat database which will store all participant baseline and 12-month questionnaire data. The University of Chicago team members will have access to this data to score select surveys (see REDCap database above).

#### Questionnaires

We will collect baseline and 12-month participant questionnaires, baseline and 12-month PCP questionnaires, and a 12-month medical office staff questionnaire. To develop the participant questionnaires, the study team compiled all items in existing instruments such as the PAM [33], PROMIS [36, 37], and BSI-18 [38]. The study team also included modified items from a mammography screening tool [35], items developed based on Aizen’s Theory of Planned Behavior [34], CFIR items developed with the input of an expert on the study PCP advisory board [16], and other items designed to capture all significant variables such as CRC screening completion, moderator and mediator data, and cost information.

To create the primary care provider questionnaires, the study team modified an 18-item survey which was previously administered to measure family physician knowledge regarding the care of childhood cancer survivors [14]. The study team edited this questionnaire to include CFIR items and questions to measure key demographic variables [16]. The medical office staff questionnaire was designed by the study team to gather additional feedback on the implementation of the intervention from the helpful perspective of a staff member working alongside the PCPs. All questionnaires were reviewed by the study PCP advisory board which includes many clinician-researchers, two psychologists, multiple primary care providers, a research nurse with expertise in CFIR, a cancer survivor/social worker, among other experts.

#### Interviews

We will conduct structured interviews with 20 primary care providers, 20 medical office staff, and up to 20 participants from each intervention arm to collect data on the implementation process (see Implementation Outcome section above for more details). We used the CFIR to guide the creation of the interview guides [16]. All interviews will be transcribed using Temi, and the transcription will be uploaded into the REDCap database.

#### Medical record reports

CRC screening reports for participants who note that they had a colonoscopy and/or multitarget stool DNA test will be obtained by contacting the ordering provider. In the 12-month questionnaire, participants will be asked to provide contact information for the healthcare provider who ordered their CRC screening. Study personnel will obtain the CRC screening reports and input the data into the REDCap database.

#### CCSS data

Age, gender, diagnosis of chronic health conditions, and race/ethnicity data for enrolled participants will be provided from previously collected data by the CCSS [17]. Since all ASPIRES study participants were previously enrolled on the CCSS, we have access to data from the surveys administered as part of this study. The CCSS Statistics and Data Center at Fred Hutchinson will send this data via a spreadsheet to the ASPIRES study statistical team at Memorial Sloan Kettering Cancer Center.

#### Study logs

Study personnel will track the cost of intervention components (e.g., material creation, text message design, personnel time to accomplish key tasks etc.) via a study log spreadsheet.

### Data analysis plan

#### Primary efficacy analysis

The primary analysis involves comparing the proportion of participants who report obtaining a colonoscopy or negative multitarget stool DNA test report or positive multitarget stool DNA test report in combination with a confirmed colonoscopy (completed screening test) in each intervention arm to the control arm. To account for the randomization strata and the sampling scheme, this difference will be estimated by taking a weighted average of the differences in stratum-specific proportions. The test of the difference in proportions will be done using a Cochrane-Mantel-Haenszel test [40].

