### Conceptual framework

The ASPIRES study is guided by the Patient Activation Model [18], which suggests that activated patients are better prepared to participate in self-management. Patient activation is the degree to which an individual understands they must play an active role in managing their own health and health care, and the extent to which they feel able to fulfill that role [19]. Individuals with higher levels of patient activation are more likely to undergo screening [20]. Activation involves four stages: (1) believing that taking an active role as a patient is important; (2) having the confidence and knowledge necessary to take action; (3) taking action to maintain and improve one’s health; and (4) staying the course even under stress [18].

Although the Patient Activation Model is a vital component of our conceptual model, we will include other important variables, many of which are from the Health Belief Model [21, 22] and the Transtheoretical Model [23–27]. These variables include benefits and barriers to screening; implementation intentions; perceived seriousness of susceptibility to CRC; and self-efficacy.

The ASPIRES study is enhanced by direct health care provider activation. PCP activation is designed to increase provider knowledge about the high-risk status of childhood cancer survivors and national screening recommendations, improve the motivation to discuss with, and order testing for, their patients, and facilitate effective information exchange and communication [28, 29]. We will examine specific factors (i.e., years in practice, location, knowledge) that may impact PCP activation.

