
### Study participants

#### Eligibility

We plan to enroll 315 participants on the study. To confirm eligibility, participants will complete an eligibility survey. Participants must meet the following criteria in order to enroll on the study: 1) have previously enrolled in CCSS, 2) age > 30 years old, 3) were treated with radiation to the abdomen, pelvis, spine, or total body irradiation, 4) no history of CRC, 5) no family history of CRC, 6) have not had a colonoscopy in the last 5 years or multitarget stool DNA test in the last 3 years, 7) have a smartphone, 8) reside in the United States, and 9) speak English.

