### Sample size and power

The primary aim involves two pair-wise comparisons of equal importance. We fix the probability of a Type I error at 0.025 for each comparison in order to maintain the overall probability of a Type I error at 0.05. We powered the study to detect a difference of 20% for each pair-wise comparison, assuming equal randomization to each of the three arms, and that approximately 20% of participants in the control arm will be adherent with recommended CRC screening. Table 5 shows the power we expect to have using two-sided Cochrane-Mantel-Haenszel tests and indicates that we should have sufficient power to detect a clinically meaningful difference even if the proportion of participants in the control arm with the primary endpoint is somewhat different than we expect.

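### The primary comparison uses no baseline prognostic factor beyond the age stratum and the sampling scheme; adjusting for three or four baseline scores already collected would be a cheap, modest gain in power, not the repair of an error

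*Protocol article*

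**What the plan says.** The Primary efficacy analysis section sets both estimate and test. The estimate is a weighted average of stratum-specific differences in proportions, chosen to reflect the randomisation strata and the sampling scheme. For the test: "The test of the difference in proportions will be done using a Cochrane-Mantel-Haenszel test". Study design gives age (30–44 and 45 or over) as the only stratification factor. Recruitment says that racial minorities will be oversampled.

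Sample size and power uses the same test ("using two-sided Cochrane-Mantel-Haenszel tests"), so the planned test and the sample size agree.

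On baseline information, the Conceptual framework says: "Individuals with higher levels of patient activation are more likely to undergo screening". REDCap database says that the PROMIS, PAM and BSI-18 "surveys are components of the participant baseline and 12-month questionnaires", and Study design has all participants completing a baseline questionnaire. The text after Table 3 adds sociodemographics and current health to the baseline and 12-month questionnaires. In the planned analyses, factors of this kind serve the moderator and mediator work, not the primary comparison.

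**The concern.** The intervention is built on patient activation. The article says that activation goes with screening, and it measures activation at baseline. If that link holds among these survivors, part of the outcome variation within each arm is predictable from data in hand, and the primary comparison treats it as noise. Chance imbalance between arms on those scores also goes uncorrected.

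This would matter little in a heavily powered trial. Here power is modest at the assumed control rate, lower if the control rate is higher, and lower again if some 12-month self-reports are missing.

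**Working it through.** **Inputs from the article.** "We plan to enroll 315 participants on the study", which at equal allocation is 315/3 = 105 per arm. "We fix the probability of a Type I error at 0.025 for each comparison", two-sided, so z = 2.2414. "We powered the study to detect a difference of 20% for each pair-wise comparison", with "approximately 20% of participants in the control arm will be adherent with recommended CRC screening", hence 20% v 40%. Table 5 is not shown, so there is no stated power figure to reproduce.

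**Step 1: base power (pooled-variance two-proportion formula).** Mean proportion 0.30.
- SE under the null: √(2 × 0.30 × 0.70 / 105) = 0.0632
- SE under the alternative: √((0.20 × 0.80 + 0.40 × 0.60) / 105) = 0.0617
- Power: Φ[(0.20 − 2.2414 × 0.0632) / 0.0617] = Φ(0.94) = 82.7%

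With the same 20-point difference, power is 79.2% at a 25% control rate and 76.8% at 30%. Power of 80% at 20% v 40% needs 99 per arm (297 in all), so 315 leaves roughly 5% for loss.

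**Step 2: what covariates could add in principle.** If baseline covariates explain a share R² of outcome variance within arm, the effective size is about 105/(1 − R²). R² is assumed; the article gives none.

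| Assumed R² | Effective n per arm | SE of risk difference | Power |
|---|---|---|---|
| 0 | 105.0 | 0.0617 | 82.7% |
| 0.02 | 107.1 | 0.0611 | 83.6% |
| 0.05 | 110.5 | 0.0602 | 84.8% |
| 0.10 | 116.7 | 0.0586 | 86.8% |
| 0.15 | 123.5 | 0.0569 | 88.8% |

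For scale, one covariate with an odds ratio of 1.5 per SD gives roughly R² = (ln 1.5)² × 0.30 × 0.70 = 0.03. The lower rows of the table therefore need several useful covariates or one strong one.

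**Step 3: simulation of a usable version.** 105 per arm, 20% v 40%, two-sided 0.025, logistic model with arm, age stratum and four covariates, standardised (g-computation) risk difference, degrees-of-freedom-corrected SE, 4,000 trials per setting.

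| Four covariates, of which | Adjusted | CMH | Difference (points) |
|---|---|---|---|
| none prognostic | 83.9% | 83.5% | 0.4 |
| one, OR 1.5 per SD | 84.7% | 83.2% | 1.5 |
| two, OR 1.5 per SD | 85.4% | 82.8% | 2.6 |
| all four, OR 1.5 per SD | 88.0% | 83.2% | 4.8 |

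The 0.4 in the first row cannot come from prognostic information. It shows how much of each difference reflects the form of the test and simulation noise. A further run of the same design gave 83.4–87.9% adjusted against about 83% for CMH.

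**Step 4: what it can cost.** The nominal level is 2.5%; with 4,000 null trials the Monte Carlo SE is √(0.025 × 0.975 / 4,000) = 0.25 points.
- Four covariates, uncorrected SE: size 2.9–3.3% across the runs.
- Four covariates, corrected SE: 2.7–2.9% in one set of runs and 2.2–3.1% in another.
- CMH in the four-covariate runs: 2.2–2.8%.
- Ten covariates, at most one prognostic, uncorrected SE: 3.5–4.0%. With ten pure-noise covariates the true SD of the estimate rose from 0.0633 to 0.0649, while the mean estimated SE was only 0.0597.
- Four pure-noise covariates: the SD moved only from 0.0614 to 0.0620.

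A short list with a corrected SE costs little even if badly chosen. A long list without correction does not hold the type I error.

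**The case against.** The strongest reply is that nothing is wrong. Stratified randomisation, a stratified risk difference, a CMH test and a sample size computed for that test form a coherent and valid plan. That stands in full: there is no bias, no type I error problem and no contradiction to repair.

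Four stronger readings are tempting, and the article does not support them.
- A reader might infer that age is all the analysis accounts for. The section also names the sampling scheme, and any replacement must keep that.
- A reader might infer that the baseline scores are strong predictors. The statement on activation is general and carries no effect size, and the Effectiveness outcomes section says only that the measured factors may be associated with completion. With R² at 0.02–0.05 the formula gives about 1 to 2 points of power.
- A reader might infer that adjustment is free. Step 4 shows otherwise.
- A reader might infer that adjustment makes up for missing outcomes. It recovers some precision but does not address who fails to respond. Nor is there clearly no allowance for loss, since no target power is visible and 315 is compatible with 80% power and about 5% loss.

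Two practical objections also stand. The article does not say that the baseline questionnaire precedes randomisation, so eligibility of each covariate must be checked. The unseen analysis plan may already contain adjusted sensitivity models, and the moderator section's first-order logistic models already yield adjusted arm effects as secondary results. Neither changes the primary test, which is fixed here.

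**Conclusion.** The point holds as a cheap improvement. The primary comparison uses no baseline prognostic factor beyond the age stratum and the sampling scheme, while plausible predictors are already being collected. From a base of about 83%, the expected gain is about 0 points if the covariates are uninformative, 1 to 3 points with one or two at an odds ratio of 1.5 per SD, and about 5 points with a stronger set.

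These figures assume 105 analysed per arm, 20% v 40%, and prognostic strengths that are assumptions, because the article gives none. The conclusion does not depend on the exact value: with a short pre-named list and a corrected SE, the possible loss is very small and the possible gain modest.

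**What to change.** Before unblinding, name three or four baseline covariates confirmed as collected before randomisation, for example PAM and PROMIS self-efficacy with one or two sociodemographic items. Make the primary estimate a standardised (g-computation) risk difference from a logistic model with arm, age stratum and those covariates. A plain logistic coefficient would change the target to a conditional odds ratio, so the standardisation step should be written in.

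Keep the sampling-scheme adjustment and the 0.025 level for each comparison. Specify a robust SE with a small-sample (degrees-of-freedom) correction, state a simple rule for missing baseline values, and retain the age-stratified CMH test as a sensitivity analysis.

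The cost is analysis-plan wording and slightly more analysis work; no new data are needed. The list should stay short, because the type I error inflation seen with ten covariates and an uncorrected SE is the main way this change could do harm.

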#### CFIR analysis

For the CFIR quantitative data, we will calculate a mean score of each statement and compare the arm differences using ANOVA (Analysis of Variance) [16]. For the CFIR qualitative data, we will use a template analysis approach to code and organize the data. Template analysis is a form of thematic analysis that emphasizes the use of hierarchical coding but balances a relatively high degree of structure in the process of analyzing text data with the flexibility to adapt it to the needs of a particular study [41]. We will develop a codebook, which will include CFIR constructs. The codebook will provide the operational definition of each code, and the inclusion and exclusion criteria. The coder will interpret the data first and then apply the CFIR code that reflects a potential barrier or facilitator being described. We will have four different coders who have experience in qualitative research to code the same data. In addition, we will evaluate the interrater reliability. The four coders will meet to discuss and reach a consensus on any coding discrepancies. Finally, using a convergent mixed-methods approach [42], we will merge the quantitative and qualitative data, organized by the 5 CFIR domains to evaluate which constructs were associated with, or more prevalent among patients who had colonoscopy or multitarget stool DNA test and those who did not (test yes v. test no), those who had positive multitarget stool DNA test and had a colonoscopy and those who did not complete a colonoscopy, and those whose PCPs ordered a test and those who did not (regardless of whether a survivor had a test); this will allow us to comprehensively evaluate facilitators and barriers to ordering and completing CRC screening to make recommendations for future adaptation and sustainability.

#### *Moderators and mediators* analysis

Since our outcome variable is dichotomous (screened or not screened), we will use logistic regression to assess the moderator effect of these characteristics on the relationship between the intervention and the primary outcome: log [Pi (1 – Pi)] = β0 + β1X + β2Z + β3 XZ + e, where Pi is the probability for patient i, β1 is the coefficient of the predictor X, β2 is the coefficient of the moderator Z, β3 is the coefficient of the product term XZ, and e is the error. We will use the likelihood ratio test to compare the nested models (the first-order model log [Pi (1 – Pi)] = β0 + β1X + β2Z + e and the higher-order model log [Pi (1 – Pi)] = β0 + β1X + β2Z + β3 XZ + e). The change in the − 2 Log Likelihood (−2LL) will be examined to see whether adding the product term to an existing additive regression equation would significantly increase the predictability. When the change is significant, a moderator effect is considered.

To explore the mediator effect, we will follow MacKinnon et al’s [43] recommendations and examine potential factors in a post hoc manner. We will use fit path analysis models using the statistical packages LISREL or EQS, inspect path coefficients, and choose the appropriate statistical tests of mediating effects according to MacKinnon et al. [43]. We may also consider testing model equivalence to examine whether the mediating path model is equivalent across the control and intervention arms. While several different tests have been used to test mediating factors, MacKinnon et al. [43] recommend using tests developed from the product of coefficients methods, where the parameters are estimated using regression, and the standard error of their product is obtained by the delta method. This test can be readily implemented using software made available by MacKinnon et al. [43]. All analyses will be adjusted for the stratification factors used at randomization.

